## Abstract

**Introduction:**

Anhedonic depression is a subtype of depression characterized by deficits in reward processing. This subtype of depression is associated with higher suicide risk and longer depressive episodes, underscoring the importance of effective treatments. Anhedonia has also been found to correlate with alterations in activity in several subcortical regions, including the caudate head and nucleus accumbens. Low intensity focused ultrasound pulsation (LIFUP) is an emerging technology that enables non-invasive stimulation of these subcortical regions, which were previously only accessible with surgically-implanted electrodes.

**Methods:**

This double-blinded, sham-controlled study aims to investigate the effects of LIFUP to the left caudate head and right nucleus accumbens in participants with anhedonic depression. Participants in this protocol will undergo three sessions of LIFUP over the span of 5–9 days. To investigate LIFUP-related changes, this 7-week protocol collects continuous digital phenotyping data, an array of self-report measures of depression, anhedonia, and other psychopathology, and magnetic resonance imaging (MRI) before and after the LIFUP intervention. Primary self-report outcome measures include Ecological Momentary Assessment, the Positive Valence Systems Scale, and the Patient Health Questionnaire. Primary imaging measures include magnetic resonance spectroscopy and functional MRI during reward-based tasks and at rest. Digital phenotyping data is collected with an Apple Watch and participants' personal iPhones throughout the study, and includes information about sleep, heart rate, and physical activity.

**Discussion:**

This study is the first to investigate the effects of LIFUP to the caudate head or nucleus accumbens in depressed subjects. Furthermore, the data collected for this protocol covers a wide array of potentially affected modalities. As a result, this protocol will help to elucidate potential impacts of LIFUP in individuals with anhedonic depression.

## 1 Introduction

Anhedonic depression is a subtype of depression characterized by an array of deficits in reward processing, including reduced enjoyment of activities and rewarding events (Serretti, 2023). The presence of anhedonia in patients with major depressive disorder is associated with longer depressive episodes, greater illness severity, and increased suicidality (Gabbay et al., 2015; Ducasse et al., 2018; Auerbach et al., 2022). In addition to its association with worsened illness prognosis, anhedonia has been found to respond less reliably than negative affective symptoms to standard psychotherapeutic and psychiatric treatments for depression (Dunn et al., 2020; Craske et al., 2024). Anhedonia's unreliable response to treatment is especially problematic given that prior analyses of patient perspectives has found that many patients view the return of positive affect to be a critically important factor in recovery from depression (Zimmerman et al., 2006; Cummergen et al., 2022). This demonstrates the critical need for improved, targeted treatments for anhedonic symptoms in patients with anhedonic depression.

Low intensity focused ultrasound pulsation (LIFUP) is an emerging brain stimulation technique that shows potential to stimulate subcortical brain regions non-invasively. Preliminary data have demonstrated that when administered within the FDA safety guidelines for ultrasound in soft tissue, LIFUP is capable of reversibly modulating neural activity without causing damage to tissue (Pasquinelli et al., 2019). Furthermore, it is able to modulate deep brain regions with high spatial specificity (Kuhn et al., 2023; Chou et al., 2024; Pellow et al., 2024; Riis et al., 2024a,b). While surgical deep brain stimulation (DBS) to reward-related subcortical regions, such as the caudate and nucleus accumbens, has been shown to be efficacious for the treatment of anhedonic depression, it is highly invasive, requiring major brain surgery that poses significant risk of complications (Fenoy and Simpson, 2014; Figee et al., 2022). This makes LIFUP an intervention of interest for anhedonic symptoms, as it is able to non-invasively stimulate these same deep brain regions in a non-invasive manner.

Investigating LIFUP in Anhedonic Depression (ILIAD) is a complementary interventional study to a broader observational study: Operationalizing Digital PhenoTyping in the Measurement of Anhedonia (OPTIMA). These two studies are distinct and have only partially overlapping subject populations; while OPTIMA recruits participants across the spectrum of anhedonia severity, ILIAD only enrolls participants with high levels of anhedonia. Additionally, ILIAD recruits from both the OPTIMA subject pool and from external sources. However, many elements of the two studies are harmonized in order to facilitate potential merging of data. Both of these studies are performed in the Wellcome Leap Multi-Channel Psych Consortium, a broader multi-site program that seeks to develop integrated models of anhedonic depression.^1^

This sham-controlled, double-blinded study investigates the impact of multiple sessions of LIFUP targeting either the left caudate head or right nucleus accumbens on an array of anhedonia-related self-report and neuroimaging measures. The two targets for this study were selected due to the literature implicating them in the pathophysiology of anhedonic depression and their central role in mesolimbic reward circuitry (Haber and Knutson, 2010; Wang et al., 2021). Reduced caudate volume has been found to correlate with anhedonia severity, and both the nucleus accumbens and the caudate have been found to have significantly weaker reward responses in individuals with major depressive disorder when compared to healthy controls (Pizzagalli et al., 2009). The left caudate in particular was selected for this study due to literature suggesting that a longitudinal increase in left caudate connectivity with the bilateral superior frontal gyrus may correlate with anhedonia improvement over the same time period (Yang et al., 2022). The right nucleus accumbens was chosen based on literature showing a correlation between anhedonia severity and altered right nucleus accumbens connectivity (Liu et al., 2021). However, the right nucleus accumbens was removed from this study midway through due to funding changes.

A handful of studies have investigated the effect of DBS to the caudate on depressive symptoms. While the one study to-date of caudate DBS in individuals with major depression as their primary diagnosis found a lack of response, this study only tested caudate DBS in individuals for whom a similar-duration trial of nucleus accumbens DBS had already failed (Millet et al., 2014). In contrast to these findings, a study of caudate DBS in an individual with severe treatment resistant obsessive-compulsive disorder (OCD) and concomitant major depression observed remission of major depressive symptoms within 6 months of implantation, well-before remission of OCD symptoms was observed (Aouizerate et al., 2004). This suggests that the caudate may merit further investigation as a potential target for deep brain stimulation in depressive disorders.

DBS of the nucleus accumbens has also been found effective for depression, with one study finding a 50% response rate in participants with severely treatment-resistant depression in which an average of eight prior medical treatments had failed to sufficiently alleviate symptoms, including psychotherapy and electroconvulsive therapy (Bewernick et al., 2010). Additionally, nucleus accumbens DBS has been found to rapidly impact symptoms of anhedonia in depressed patients (Schlaepfer et al., 2008). Given this literature, the nucleus accumbens is a promising potential target for non-invasive brain stimulation with LIFUP.

Our study is the first to investigate the effects of LIFUP to the caudate and nucleus accumbens in individuals with anhedonic depression. However, preliminary studies in other populations have demonstrated the safety and feasibility of LIFUP to these regions. A recent study of LIFUP to the caudate in two veterans with post-traumatic headache observed reduced pain levels after several sessions (Yoon et al., 2024). Additionally, a study of long-term repeated administration of LIFUP to the caudate and putamen in non-human primates showed a slight but significant increase in motivation and task accuracy (Munoz et al., 2022). Stimulation of the nucleus accumbens using LIFUP has been found to reduce substance cravings in participants with substance use disorder and to increase connectivity between the nucleus accumbens and medial prefrontal cortex in healthy controls (Mahoney et al., 2023; Peng et al., 2024). Several other studies have also found beneficial effects of LIFUP to other brain regions in depressed participants, namely the subcallosal cingulate cortex and frontotemporal cortex (Reznik et al., 2020; Riis et al., 2024a,b).

Through this double-blinded, sham-controlled study, we hope to gain a better understanding of the feasibility and potential effects of LIFUP stimulation to the caudate head and nucleus accumbens in individuals with anhedonic depression. The study utilizes a wide array of self-report, digital phenotyping, and neuroimaging metrics in order to obtain a maximally comprehensive picture of the potential effects of LIFUP.

## 2 Materials and methods

### 2.1 Subject population

This protocol will enroll up to 100 right-handed adult participants with high anhedonia and moderate or high depression, with the goal of achieving an evaluable sample of at least 40 participants. For the purposes of this protocol, evaluable participants are defined as those who complete all three LIFUP sessions, both MRI scans, and at least one outcome measure after completing LIFUP.

#### 2.1.1 Inclusion/exclusion criteria

A complete list of inclusion/exclusion criteria for this study is available in Table 1.

**Table 1 T1:** Inclusion and exclusion criteria.

**Inclusion criteria**	**Exclusion criteria**
Age 18–65	Current tobacco smoker of >11 cigarettes/day or the nicotine equivalent
Fluent in English	Current report of alcohol or substance abuse or dependence
Right-handed	Recent changes in antidepressant dosing or medication (dose and medication need to be stabilized within the last 2 weeks)
Healthy or corrected to healthy vision	Reported diagnosis of schizophrenia or psychotic symptoms
Residing in Los Angeles area for the duration of study	Currently taking benzodiazepines, or taken benzodiazepines in the past 8 weeks
Own functioning iOS smartphone (iPhone 8 or later, iOS 15 or newer) with access to reliable data plan and Wi-Fi	History of medical event(s) or diagnoses likely to result in neurological abnormalities including diagnoses of Alzheimer's, Parkinson's, neurodegenerative disorders, movement disorders, reports of past seizures or stroke, or history of brain tumors or brain surgery.
Able to read and understand a written informed consent form	Medical conditions involving chronic mobility impairment including spinal cord injuries, or severe osteoarthritis of knee or hip
Willing to participate in the study and complete required tasks as outlined in study timeline, including MRI, LIFUP, Apple Watch wear, and surveys	Unwilling or unable to refrain from making significant changes to hairstyle after enrollment and before LIFUP sessions are complete (i.e., full hairstyle to shaved head, significant change in locs, etc.)
Eligible for MRI scanning and neuromodulation	Contraindications for MRI scanning, including pregnancy, metal implants, braces, significant grip impairment and claustrophobia
PVSS < 6.5 at screening and stable for ≥12 weeks, as indicated by average scores across OPTIMA protocol or by self-report for those screened from general population	Any previous treatment with electroconvulsive therapy (ECT) or deep brain stimulation (DBS) due to increased risk of seizure and unclear evidence of how LIFUP will affect individuals who have received these treatments.
PHQ scores > 10 at screening and stable for ≥12 weeks, as indicated by average scores across OPTIMA protocol or by self-report for those screened from general population	Less than 6 months since any other neuromodulation treatment such as transcranial magnetic stimulation (TMS), Vagal nerve electrostimulation, or transcranial direct current stimulation (TDCS).
If screened from OPTIMA, have completed the majority of OPTIMA assessments	Less than 6 months since prescribed ketamine infusion or other intensive, acute therapy for depressive symptoms.

#### 2.1.2 Recruitment methods

A primary recruitment source for this study is the UCLA OPTIMA study. Study staff screen participants from OPTIMA who have consented for future contact for research and appear eligible based on their self-reported depression and anhedonia scores. The study is also recruiting individuals from the Los Angeles area based on self-reported depression and anhedonia scores.

#### 2.1.3 Participant retention

In order to promote participant retention, reminders for visits are sent throughout the study via e-mail, text message or phone call. Additionally, participants receive a final reminder about their in-person visits 24 h before each scheduled visit.

## 3 Data collection and intervention

For an overview of the timeline of data collection and intervention procedures described below, please refer to Figure 1.

**Figure 1 F1:**
[figure not shown]
Study timeline. **Pink (bottom left)**: OPTIMA participants only. **Purple (top left)**: Non-OPTIMA participants only. **Blue (right)**: all participants.

### 3.1 Intervention protocol

#### 3.1.1 Condition assignment

Following screening and enrollment, participants are block-randomized to one of two conditions at equal rates: (1) active stimulation to the left caudate or (2) sham stimulation to the left caudate. A previous version of this protocol block-randomized participants into three conditions at equal rates: (1) active stimulation to the left caudate head, (2) active stimulation to the right nucleus accumbens, or (3) sham (assigned to left caudate or right nucleus accumbens to maintain concealment of conditions); however, due to budget changes, randomization to the “active stimulation to the right nucleus accumbens” condition was removed; a total of six participants were assigned to the active nucleus accumbens condition prior to its removal.

#### 3.1.2 LIFUP intervention

Participants receive the appropriate LIFUP intervention at each of three sessions; each session is spaced 2–4 days apart from the last, such that sessions occur at a minimum schedule of days 1, 3, 5 and at a maximum schedule of days 1, 5, 9. At each of these sessions, LIFUP is administered in ten 30-s sonications, with 30 s gaps between each sonication. LIFUP parameters are 5 ms pulse width, 100 Hz pulse repetition frequency, 50% duty cycle, ISPTA.3 720 mW/cm^2^, ISPPA.3 14.4 W/cm^2^. These parameters were selected due to previous literature suggesting that a 50% duty cycle can achieve excitatory effects (Zhang et al., 2021). The transducer is aimed at the appropriate target using BrainSight neuronavigation (BrainSight, Rogue Research, Montreal, Quebec, Canada) with a participant's T1-weighted structural scan. LIFUP is administered using the Brainsonix BX Pulsar 1002 focused ultrasound device with a 55, 65, or 80 mm transducer, depending on what depth is needed to reach the target for a given participant based on individual anatomy (Schafer et al., 2021). To minimize ultrasound energy exposure to air, a gel pad and water-based ultrasound gel are placed between the transducer and the participant's scalp. For active sonication, the transducer is used with a gel pad that allows the ultrasound energy to pass through; for sham sonication, the transducer is used with a gel pad that blocks ultrasound energy. Participants are asked to sit comfortably and remain still for the duration of the 10-min sonication procedure. If a participant expresses discomfort at any point, they are given the option to stop the procedure.

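### The stated ultrasound intensities disagree tenfold: 14.4 W/cm² pulse-average at a 50% duty cycle gives 7,200 mW/cm² time-average, not 720 mW/cm²

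*Protocol article*

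**What the plan says.** Section 3.1.2 (LIFUP intervention) describes one set of settings, used at each of three sessions: "5 ms pulse width, 100 Hz pulse repetition frequency, 50% duty cycle, ISPTA.3 720 mW/cm^2^, ISPPA.3 14.4 W/cm^2". Each session has ten sonications of 30 s with 30 s pauses between them, and the same section calls this a 10-minute procedure. Active and sham differ only in the gel pad.

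The reason given for the settings is "previous literature suggesting that a 50% duty cycle can achieve excitatory effects". Section 4.1 then builds the clinical hypothesis on exciting underactive striatal regions.

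On safety, the Introduction says that preliminary data show reversible modulation without tissue damage "when administered within the FDA safety guidelines for ultrasound in soft tissue". It gives no numerical limit. No other section restates, defines or corrects the intensities.

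**The concern.** The two intensities are linked by the duty cycle, so any two of the three fix the third. Here the third does not follow from the other two.

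What is at stake is the dose of the sole intervention:

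- **Exposure.** A reader cannot tell whether the time-average intensity is 720 or 7,200 mW/cm², or whether the pulse-average intensity is 14.4 or 1.44 W/cm². The trial cannot be replicated, or its result tied to a dose, until this is settled.
- **Mechanism.** If the two intensities are the correct figures, the duty cycle is 5% and the stated argument for excitation no longer applies to this trial.
- **Safety.** The Discussion hopes to show that multi-session LIFUP is safe, which requires a known exposure. Section 3.8.4 dispenses with a data monitoring committee because risk is held to be low, and section 3.8.6 does not actively solicit adverse events. With oversight this light, the stated exposure should be unambiguous.

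**Working it through.** **Inputs, all from section 3.1.2**

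| Quantity | Stated value |
|---|---|
| Pulse width | 5 ms |
| Pulse repetition frequency | 100 Hz |
| Duty cycle | 50% |
| Time-average intensity (ISPTA.3) | 720 mW/cm² = 0.720 W/cm² |
| Pulse-average intensity (ISPPA.3) | 14.4 W/cm² |
| Pattern per session | ten sonications of 30 s, 30 s gaps |

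**Step 1: duty cycle from the timing figures.** Duty cycle = pulse width × repetition frequency = 0.005 s × 100/s = 0.50. This reproduces the stated 50%, so the three timing figures agree.

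**Step 2: time-average intensity within a pulse train.** ISPTA = ISPPA × duty cycle = 14.4 × 0.50 = 7.2 W/cm² = 7,200 mW/cm². The ratio to the stated value is 7,200/720 = 10.0. Both intensities carry the same .3 derating, so it cancels in the ratio.

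**Step 3: does averaging over the gaps close the difference?** Total time on is 10 × 30 s = 300 s.

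| Averaging window | Calculation | Result (mW/cm²) | Ratio to 720 |
|---|---|---|---|
| Within a sonication | 7,200 × 1 | 7,200 | 10.0 |
| Ten sonications, nine gaps (300 + 270 = 570 s) | 7,200 × 300/570 | 3,789 | 5.3 |
| 600 s (equivalently 30 s on, 30 s off) | 7,200 × 300/600 | 3,600 | 5.0 |

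To reach 720, the window would have to be 7,200 × 300/720 = 3,000 s, or 50 minutes. The document mentions no such window.

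**Step 4: what would make the set consistent?**

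- Keep the timing and ISPPA.3: ISPTA.3 becomes 7,200 mW/cm².
- Keep the timing and ISPTA.3: ISPPA.3 becomes 0.720/0.50 = 1.44 W/cm².
- Keep both intensities: the duty cycle becomes 0.720/14.4 = 0.05, or 5%. That needs 0.5 ms pulses at 100 Hz (0.05/100 s) or 5 ms pulses at 10 Hz (0.05/0.005 s), for example.

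The first two options change one figure. The third changes at least two, because the stated duty cycle and at least one of pulse width and repetition frequency must both move.

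**The case against.** The arithmetic has no good defence. All five figures stand in one clean sentence, with no sign of redaction or a broken table. The fair objections concern how far the point reaches.

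- **It is a contradiction in reporting, not evidence of what was delivered.** This stands. 720 and 14.4 fit each other exactly at 5%, and the three timing figures fit each other exactly at 50%. The intensity pair may have been carried over from a 5% setting, or one intensity may be misstated by a factor of ten.
- **The text favours 50% as intended.** This also stands. The duty cycle is supported by pulse width and repetition frequency and is named as the reason for the choice, so the doubt falls more on the intensities. The excitation argument fails only if the timing figures are the wrong ones.
- **The Introduction's safety sentence describes earlier data.** Correct. It does not say that these settings comply with a limit, and it quotes none. The link to this trial's safety is an inference, and no breach is shown.
- **The comparison of active with sham is not biased.** Also correct. One set of settings is stated and the arms differ by gel pad, so no endpoint or test is affected.

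None of this removes the need for a correction. It bears on which figure to change and on how the consequences are worded.

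**Conclusion.** The concern holds, and the settings must be corrected. As written, at least one of the five is wrong. The discrepancy is a factor of 10 within a pulse train and 5.0 to 5.3 if the pauses are averaged in. The implied duty cycle is 5% against the stated 50%.

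This rests on the standard relation between the two intensities and on both carrying the same derating, as their labels show. It does not depend on any outside safety limit. If exactly one figure is wrong, it must be one of the two intensities, because the timing figures agree with each other. The document alone cannot say which figure to change. The weight of the finding comes from the undefined dose of the sole intervention, not from a demonstrated safety breach or a threat to the planned analyses.

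**What to change.** 1. Reconcile pulse width, repetition frequency, duty cycle, ISPTA.3 and ISPPA.3 against the device logs and the output calibration.
2. State the interval over which ISPTA.3 is averaged: within a sonication, or across sonications and pauses.
3. Correct whichever figure is wrong in section 3.1.2 and in any other trial document that carries it.
4. Confirm from the logs that all treated participants received one set of settings. The document gives no sign that they did not, but the logs will be open for step 1 anyway.
5. If the reconciled duty cycle is not 50%, rewrite the excitation rationale in section 3.1.2 and the hypothesis in section 4.1 that depends on it. If the reconciled ISPTA.3 is not 720 mW/cm², say explicitly how the delivered exposure stands against the guideline that the Introduction invokes.
6. If the delivered exposure differed from the approved one, notify the ethics board.

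The cost is a check of device records and a corrected statement. The design, sample size and analysis do not change.

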#### 3.1.3 Randomization and blinding

Active and sham conditions are concealed through the use of a set of identical gel pads factory-designated solely as A or B. The active and sham gel pads are visually identical to maintain blinding, and the retailer providing the gel pads (BrainSonix Corp., Sherman Oaks, California, United States) will maintain condition concealment until after the conclusion of the study. Staff are only informed which gel pad to use with blinded labels (A or B) and conduct all appointment procedures the same regardless of condition. As a result, staff performing the intervention, study investigators, and study participants all remain blinded to condition assignment. Participants are never informed if they received active or sham interventions. Condition assignments may be selectively revealed to research investigators and staff by steering committee consensus, when data analysis or research operations and monitoring require that conditions be known.

Randomization is performed via computer-generated random sequencing with blocking to reduce cohort effects. In the REDCap database, research staff are provided with a “randomize” function within each record, which provides them with condition assignment (i.e., gel pad A or B) after the command is executed.

The initial design of this study utilized three gel pads, one of which was sham. Participants in both the nucleus accumbens and caudate group were randomized to gel pads A, B, and C at equal rates, such that 1/3 of participants would receive active caudate, 1/3 would receive active nucleus accumbens, 1/6 would receive sham caudate, and 1/6 would receive sham nucleus accumbens. When it was determined due to funding changes that the study design should be reduced to two conditions, one individual on the team was unblinded by steering committee consensus. This individual then performed analyses on the imaging data from the Card Guessing Task to determine changes in reward attainment and anticipation across LIFUP in each group in order to guide a data-informed decision on which condition to keep in the study. Results of the analyses were then presented to the investigative team, keeping conditions concealed. Based on these results, investigators chose a condition to keep in the revised protocol, and an alternate condition was designated to keep in the case that the primary choice was sham. Investigators were informed that the nucleus accumbens target would be removed, but were not informed which group in the presented analyses was the active caudate group. The only individuals who were knowledgeable about condition assignment were the individual who performed the analysis and the research program manager who supervised the staff performing LIFUP. Conditions remained concealed to all other members of the research team. A total of six participants received active nucleus accumbens LIFUP prior to the removal of this condition.

To maximize the integrity of blinding, outcome assessors refrain from making any guesses regarding active/sham conditions. In the case where a participant guesses their condition based on how they feel during sessions, staff listen to their thoughts but refrain from discussion, and no records of these guesses are kept.

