#### 3.8.5 Research operations team

This study is being performed by research operations staff under the UCLA Depression Grand Challenge. The research operations project director provides supervision of study operations and ensures adherence to departmental standards. The project manager is responsible for protocol implementation, management of IRB submissions and study documents, database maintenance, data quality control, data monitoring, and study reporting. The research coordinator is responsible for participant screening, enrollment, and communication, as well as data collection and management. A team of research assessors is responsible for MRI data collection and managing participants in the MRI environment, as well as conducting LIFUP administration. Informatics specialists are an integral part of this protocol, as they are responsible for the management and storage of the multitude of data types, including digital sensing data, survey data, and scan data. Informatics specialists built the study screening website and are responsible for database technical support for this protocol. The study utilizes a third party company, Avicenna (previously Ethica) for app development and hosting to collect data for digital phenotyping and Ecological Momentary Assessment (EMA). This study collects information relating to suicidal ideation, and responses to participants that indicated imminent risk are managed in collaboration with Protocall Services—a third party, 24 h call service—as well as Depression Grand Challenge licensed clinical social workers.

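### One pad letter per arm, visible to staff, means that learning one A/B participant's condition reveals it for all of them

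*Protocol article*

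**What the plan says.** All of the following is in the protocol article.

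- **Code.** Section 3.1.3: "Active and sham conditions are concealed through the use of a set of identical gel pads factory-designated solely as A or B". Section 3.1.2 explains that one type of pad transmits the ultrasound and the other blocks it, so the letter alone separates active from sham.
- **Who sees it.** After randomisation REDCap returns the letter to research staff, in a function "which provides them with condition assignment (i.e., gel pad A or B) after the command is executed". Section 3.1.2 sets three sessions per participant, so the letter is used three times.
- **Who holds the key.** The pad supplier "will maintain condition concealment until after the conclusion of the study". The same paragraph adds: "Condition assignments may be selectively revealed to research investigators and staff by steering committee consensus". It gives data analysis, research operations and monitoring as reasons.
- **What has already happened.** Section 3.1.3 reports that one team member was unblinded to analyse imaging data when the design was cut to two conditions. That analyst and the research program manager supervising the LIFUP staff were the only people who knew the assignments.
- **Impressions.** Also in section 3.1.3: "In the case where a participant guesses their condition based on how they feel during sessions, staff listen to their thoughts". Staff do not discuss these guesses and keep no record of them.
- **Staffing.** Section 3.8.5: "A team of research assessors is responsible for MRI data collection and managing participants in the MRI environment, as well as conducting LIFUP administration".
- **Earlier cohort.** "The initial design of this study utilized three gel pads, one of which was sham". The article does not say whether letters were reassigned when the study moved to two pads.

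**The concern.** A masked label protects the blind best when breaking it for one person says nothing about the next. Here the label is shared by a whole arm and is in front of the staff who handle participants. Two routes to the key follow.

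The first is disclosure. The plan permits it to investigators and staff for operational reasons, and knowledge of the conditions has already reached the supervisor of the LIFUP team. The second is pooling. If the two pads feel or sound different in any way, staff who hear participants' impressions with the letter in view can combine them across participants.

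At stake is expectancy passed on at in-person visits. The main clinical outcomes are self-ratings of mood and reward, which are open to expectancy. Because guesses go unrecorded, the described procedures leave no record of them from which a decoded letter could be noticed afterwards.

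**Working it through.** **Inputs.** Two letters, one per arm (section 3.1.3); allocation at equal rates (section 3.1.1); an evaluable target of at least 40 (section 2.1), used here only as an illustrative N. Cue accuracy q is an assumption, since the article gives no value.

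**The plan's own figure.** The only number stated on the coding is the split under the three-pad design. With two targets at 1/2 each and one sham pad in three:
- active per target = 1/2 × 2/3 = 1/3
- sham per target = 1/2 × 1/3 = 1/6
- total = 2 × 1/3 + 2 × 1/6 = 1

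This agrees with section 3.1.3. In that design, disclosing the sham pad revealed everyone, while disclosing one active pad left the other two at 50:50. With two pads, either disclosure settles everything.

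**Route 1: one disclosure.** Let each arm have k codes, N = 40, 1:1. With k = 1, learning what A means also gives B, so 40 of 40 become certain. With k of 2 or more, only those sharing the disclosed code become certain: N/(2k).
- k = 2: 40/4 = 10
- k = 5: 40/10 = 4
- k = 10: 40/20 = 2
- k = 20: 40/40 = 1 (participant-specific)

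**Route 2: pooled impressions.** Suppose each of n participants gives one impression that points to the right key with probability q, independently, and staff follow the majority. With X ~ Bin(n, q), the chance of identifying the key is P(X > n/2) + 0.5 × P(X = n/2). For q = 0.60 and n = 40 this is 0.870 + 0.028 = 0.898.

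| q (assumed) | n = 10 | n = 20 | n = 40 |
|---|---|---|---|
| 0.50 (no cue) | 0.500 | 0.500 | 0.500 |
| 0.55 | 0.621 | 0.671 | 0.736 |
| 0.60 | 0.733 | 0.814 | 0.898 |
| 0.65 | 0.828 | 0.913 | 0.973 |
| 0.70 | 0.901 | 0.967 | 0.996 |

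With participant-specific codes nothing accumulates, and staff stay at q for each person.

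**Where the exposure falls.** Section 3.7.1.1 has surveys completed through emailed links, and section 3.7.1.2 has EMA delivered by the app. Staff therefore do not administer the PHQ-14, PVSS-21 or EMA. Contact is at the LIFUP and MRI visits, which section 3.8.5 gives to one team.

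**The case against.** Several stronger readings are tempting, and the article does not support them.

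- **That selective disclosure is impossible.** The clause selects who is told and when; it does not promise to reveal single participants. Section 3.1.3 shows it being applied in that sense, with conditions kept from the rest of the team. Only selection by participant is ruled out.
- **That one disclosure unblinds the whole trial.** It unblinds the recipient for all A/B participants. It goes further only if the knowledge spreads, and participants are never told their condition.
- **That staff who know the letter collect the primary outcomes.** The self-reports are remote. For imaging, Card Guessing outcomes are predetermined and spectroscopy involves no task. One team covers LIFUP and MRI, but the article does not say that the same person does both for a given participant.
- **That experience will decode the letters.** With no cue the chance stays at 50% for any number of participants. The pads look alike and procedures are the same in both conditions. The larger figures need an informative cue, an impression from every participant and someone pooling them without records. The 40-participant column is reached only once all 40 have been heard, leaving nobody later in that illustration to influence.
- **That it covers every participant.** The first cohort used three pads, and that the letters stay fixed is inferred from the absence of any described rotation.

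These points limit the likely harm. They leave the dependence on one code per arm standing, and identical appearance does not exclude a difference in sensation, which section 3.1.3 itself anticipates by providing for guesses based on how participants feel.

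**Conclusion.** The point holds for the two-pad phase. With one letter per arm, shown in REDCap and used at each session, learning one condition gives all of them (40 of 40 against 1 of 40 under individual codes, for an illustrative 40) to anyone who sees the letters. This part needs no assumption beyond the letters keeping their meaning within the A/B phase.

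The pooling risk is conditional. At assumed accuracies of 50%, 55%, 60% and 70% it is 50%, 67%, 81% and 97% after 20 participants, and 50%, 74%, 90% and 99.6% after 40. The documents do not show which applies.

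The risk is concrete because disclosure to staff for operations is allowed and the program manager over the LIFUP staff is reported to have known the conditions. Nothing in the article shows that this knowledge reached the staff or that any result is biased. The point is a fragile safeguard that can be strengthened cheaply.

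**What to change.** For the remaining randomisations:

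1. Have the supplier, which already holds the key, label pads with non-repeating kit codes, one per participant for all three sessions.
2. Have REDCap return a kit number in place of A or B.
3. Give any analyst who needs group identity a separate dummy group label that does not appear on the participant record.
4. Keep unblinded people out of the supervision of LIFUP and MRI sessions where existing staffing allows.

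The disclosure clause can stay as it is, because its data-analysis purpose needs group-level information.

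The cost is relabelling, a revised REDCap allocation table, a short amendment and somewhat more pad inventory handling. Treatment and planned analyses do not change. Participants already treated remain under the old code, and the article does not say how many randomisations are left, so the gain depends on how soon the change is made.
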